#### Qualitative Outcomes

The qualitative outcomes of this proposed project include in-depth interviews with patients with diabetes and diabetes health care personnel and observations of consultations between diabetes health care personnel and patients participating in the digital care model. The semistructured in-depth interviews will aim to explore patients’ acceptability of digital communication and how patients and diabetes health care personnel utilize the technology. The same patients will be observed and interviewed after obtaining their written informed consent. The interview guide for patients and health care professionals can be found in Multimedia Appendices 3 and 4, respectively.

### Sample Size

The proposed study will evaluate the relevance and effects of digital services in practice without participants being randomly drawn to a control group and, therefore, excluded from the possibility of using technological solutions in clinical follow-up. Therefore, we can assume that there is a difference between patients who choose to engage in digital care and those who choose traditional health care services. It is impossible to foresee or decide how many patients will participate through the digital PROM, but we expect more patients in the group of users of the digital service. To statistically identify the similarities and differences between the groups, we consider a 10% alteration in PAM-13 to be clinically significant, such as a change of ≥4 points. To identify a clinically relevant change to this extent, a minimum of 32 participants is required in each group. To account for potential dropouts, we will continue the recruitment of participants until we have included the required number of at least 35 participants in the control group. Consenting patients will be compared based on their chosen group, that is, engaged or not engaged in digital care. If they choose to continue with standard care at the clinic, they will contribute data for comparison purposes after providing their consent. Recruitment will continue for an estimated year, or until nearly all patients in the clinic have been offered the digital solution.

We will use purposive sampling for the qualitative interviews and the observations [53] when recruiting patients and health care personnel for the qualitative study. Approximately 25 patients participating in the digital care model are regarded as sufficient. Patient participants will be included based on purposeful sampling to gain variations in age, gender, and HbA_1c_ levels. Thus, the number of patients included will depend on the findings of a constant comparative analysis. The sample size for diabetes health care personnel depends on the consenting number of health care personnel from the outpatient clinic under study.

### Analysis

#### Statistical Analysis

The baseline (T0) and follow-up (T1) variables will be descriptively presented, whereas continuous variables will be analyzed using the median and range if the data are skewed and the mean and SD for normally distributed data. Categorical data will be presented as counts and percentages. The mean change will be estimated by subtracting the baseline scores from the follow-up scores. Any differences in mean changes in short- and long-term variables will be modeled using an ANOVA. To adjust for possible confounders, logistic regression models will include age, gender, and education. We will assess the number of patients tested for eligibility, declined to participate, lost to follow-up, and included in the analysis.

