### Study Outcomes

#### Overview

The primary outcome in this study is the change in self-management, as measured through the Patient Activation Measure (PAM) questionnaire after 1 year, which will then be compared between the users and the nonusers of the digital PROM. The secondary outcomes include glycated hemoglobin (HbA_1c_), quality of life, health literacy, acceptability, health economics, and the use of health service resources. Quantitative data will be collected through patients’ self-reports and the extraction of clinical variables from patients’ medical records. In addition, data on the patients’ use of MyDignio will be extracted, including how many clinical PROMs they completed during the study period. Self-reported and clinical variables will be collected among all consenting participants, regardless of their participation in the digital solution. The standardized self-reported outcome measures are presented in Table 1.

**Table 1 table1:** Standardized self-reported outcome measures.

Domain and questionnaire and item, scale, and interpretation					Time point						
					T0		T1				

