## Results

The study received funding in March and October 2022 from Oslo Metropolitan University–OsloMet internal funding. The digital solution was implemented in clinical care at the department in November 2021, and the first participant was enrolled in the research project with a completed T0 on October 27, 2022. As of September 6, 2023, a total of 220 patients have been enrolled in the project, of which 84.5% (n=186) are digital users and 15.5% (n=34) are nonusers in the comparative group. The data collection is projected to end during 2024.

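### The ANOVA named for mean PAM change pools the variance across self-selected groups of about 186 and 34, leaving its error rate exposed to any difference in spread

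*Protocol article*

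**What the plan says.** The Study Outcomes overview defines the endpoint: "The primary outcome in this study is the change in self-management, as measured through the Patient Activation Measure (PAM) questionnaire after 1 year", compared between users and nonusers of the digital PROM. The Statistical Analysis section forms change scores as follow-up minus baseline and then names the test: "Any differences in mean changes in short- and long-term variables will be modeled using an ANOVA". It names no unequal-variance or robust version. The only covariate-adjusted model it mentions is logistic regression, which does not estimate a difference in mean change, so as written the ANOVA carries the comparison of means.

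The Sample Size section says how the groups arise: "Consenting patients will be compared based on their chosen group, that is, engaged or not engaged in digital care". It foresees unequal sizes: "we expect more patients in the group of users of the digital service". The Results section reports 220 enrolled, "of which 84.5% (n=186) are digital users and 15.5% (n=34) are nonusers in the comparative group".

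No SD of PAM change is given, either overall or by group.

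**The concern.** With two groups, an ordinary ANOVA is the pooled-variance t test. Its reference distribution is correct for a difference in means when both groups share one variance. In balanced groups a departure from that assumption does little harm. In groups of 186 and 34, the pooled variance comes mostly from the users, while the uncertainty of the difference comes mostly from the nonusers.

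If nonusers vary more in their 12-month change, the standard error is too small, the interval too narrow and the false-positive rate above 5%. If users vary more, the test is conservative and loses power. The same sentence of the plan governs the other continuous change scores (for example PAID, WHO-5 and HbA1c), so they share this sensitivity, each according to its own SD ratio.

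Nothing in the design protects against unequal spread. The groups are not randomised, and the article says "we can assume that there is a difference between patients who choose to engage in digital care and those who choose traditional health care services". Exposure among users is also not uniform: "data on the patients’ use of MyDignio will be extracted, including how many clinical PROMs they completed during the study period". These features make unequal spread possible; they do not show it.

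**Working it through.** **Inputs from the article.** Users n₁ = 186 and nonusers n₂ = 34 (Results); 186/220 = 84.5% and 34/220 = 15.5%, as printed there. Planned minimum: 32 per group, with recruitment to at least 35 controls (Sample Size).

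**Assumptions.** Two-sided 5% level, normal change scores, user SD set to 1, and nonuser/user SD ratio r varied because the article gives no SD.

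**The plan's own figure.** The 32 per group rests on this target: "we consider a 10% alteration in PAM-13 to be clinically significant, such as a change of ≥4 points". SD, alpha and power are not stated, so 32 can only be back-solved. At two-sided 5% and 80% power, SD = 4 / [(1.960 + 0.842) × √(2/32)] = 5.71. That is one common SD and says nothing about r.

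**Where the weight lies at 186:34.**
- Users' share of the pooled degrees of freedom: 185/218 = 85%.
- Nonusers' share of the variance of the difference when SDs are equal: (1/34) / (1/34 + 1/186) = 0.02941/0.03479 = 85%.

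**Standard error.**
- Pooled variance: v = (185 + 33r²)/218.
- Variance that the ANOVA uses: v × (1/186 + 1/34) = 0.03479v.
- True variance: 1/186 + r²/34.
- Approximate rejection rate when mean changes are equal: P(|Z| > 1.96k), where k = √(ANOVA variance / true variance).

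| r | v | ANOVA variance | True variance | k | Approx. rejection | Simulated ANOVA | Simulated Welch |
|---|---|---|---|---|---|---|---|
| 0.8 | 0.9455 | 0.0329 | 0.0242 | 1.166 | 2.2% | 2.3% | 5.0% |
| 1.0 | 1.0000 | 0.0348 | 0.0348 | 1.000 | 5.0% | 5.0% | 5.0% |
| 1.25 | 1.0851 | 0.0378 | 0.0513 | 0.858 | 9.3% | 9.3% | 5.0% |
| 1.5 | 1.1892 | 0.0414 | 0.0716 | 0.760 | 13.6% | 13.6% | 5.0% |

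Simulations used 200,000 replicates per setting. Coverage of the nominal 95% interval is one minus the rejection rate: 90.7% at r = 1.25 and 86.4% at r = 1.5. At the wider ratios of 0.5 and 2.0 the ANOVA rejects 0.25% and 20.8%, and Welch 5.0% at both.

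**Is the imbalance the cause?** At 32:32 the pooled test stays at 5.0 to 5.2% for every ratio from 0.5 to 2. At 186:35 and 170:32 the results are almost the same as at 186:34 (r = 1.5: 13.5% and 13.4%), so the enrolment date does not drive the answer.

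**Power.** For a true difference of 0.5 nonuser SD:
- Equal SDs: ANOVA 75.4%, Welch 73.8% (20,000 replicates), a loss of 1.6 points. A repeat with 400,000 replicates gave 76.1% and 74.7%, a loss of 1.4 points.
- User SD 1.5 times the nonuser SD: ANOVA about 44%, Welch about 67%.

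**Would a variance pretest help?** For a two-sided 5% F test on 33 and 185 degrees of freedom, power at r = 1.25 is P(F > f₀.₉₇₅/1.5625) + P(F < f₀.₀₂₅/1.5625), about 42%. It would miss such a difference more often than it found it, at a ratio where the ANOVA's error rate is already close to double.

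**The case against.** The strongest reply is that the article never says the variance will be pooled. It is a condensed account, a full analysis plan may name Welch or robust errors, and the Limitations section promises suitable methods chosen with a statistician. What stands is that pooling is the ordinary meaning of ANOVA and not a word in the text. But the article does fix a method for this comparison, and a general promise does not change it.

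Second, unequal spread has no direct support. This stands. A reader might infer from the statement that the groups differ, or from the usage counts, that the variances differ. The first concerns who chooses each route and the second only what will be recorded; neither is about the spread of 12-month change. The direction of any difference is also unknown.

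Third, a reader might say that the ANOVA's null hypothesis includes equal variances. It does not. The null concerns means, and equal variance is an assumption behind the reference distribution.

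Fourth, the 186:34 split might be read as a departure from the plan. It is not: 32 per group is given as a minimum, and more users were expected.

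Finally, confounding by self-selection is the larger threat, and Welch does nothing for it. That is correct, but it is no reason to leave the interval exposed to a second, avoidable problem.

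**Conclusion.** The point holds as a conditional vulnerability. The named test, in its ordinary form, is sensitive to unequal SDs because the groups are about 5.5 to 1 in size. If the SDs of change are equal, the ANOVA holds its 5% level. An SD difference of about a quarter between the groups would roughly halve or nearly double the error rate (2.3% at a ratio of 0.8, 9.3% at 1.25), and a ratio of 1.5 gives 13.6%. These figures rest on normal change scores, a two-sided 5% level and assumed SD ratios.

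It would be tempting to conclude that the primary p-value will be badly wrong, or that an error repeats through the secondary outcomes. The documents do not support either, because they give no SD for any outcome in either group. The change is worth making because it is cheap and removes the dependence on an assumption the design does nothing to secure.

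**What to change.** In the Statistical Analysis section, replace the ANOVA sentence with wording such as: *Differences between users and nonusers in mean change will be estimated with 95% confidence intervals that do not assume equal variances (Welch). If a linear model with covariates is used, heteroscedasticity-robust standard errors will be reported.* Specify this as the analysis from the start, not as a fallback after a significant variance test.

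The cost is one sentence and a standard software option, with no new data or patients. If the variances are equal, the loss is under 2 percentage points of power. The calculations above cover Welch only; robust errors in a covariate model were not simulated. Confounding by self-selection, and the use of logistic regression to adjust a continuous change, need their own treatment.

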### Limitations

In evaluating the implementation of digital tools and PROMs, a randomized controlled trial could be considered the gold standard to minimize confounding variables and provide stronger evidence. In this case, to design a control group, we would have to withhold the tools from patients in the clinic, which could be considered unfair clinical practice in the clinic. We could have chosen to have a control group at another hospital. However, practices in endocrinology outpatient clinics are changing, making it difficult to find a hospital department administering the usual care. Therefore, this study has been planned as an observational quasi-experimental design, with its limitations being potential confounding variables and bias. This is a novel study, and we plan to include numerous participants with a long follow-up period. We will minimize bias and confounding by including patients engaged in digital PROMs and patients choosing traditional care, controlling for known confounders, and using appropriate statistical methods to analyze data in collaboration with a statistician.

A potential limitation, according to the qualitative part of the study, is related to the conduct of the observations of consultations with patients and being interviewed about their practice, with a potential risk for reactivity of social desirability bias. Diabetes health care personnel might modify their behavior while being observed to conform to expectations about performance. Similarly, they could provide responses in the interviews that they believe are socially acceptable, rather than giving honest and accurate answers. It will be important for the researchers to establish trust and ensure that the responses are kept confidential and not used to evaluate performance.

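### The only confounder adjustment named is logistic regression, which cannot give an adjusted difference in mean PAM change, the continuous primary outcome

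*Protocol article*

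**What the plan says.** Study Outcomes (Overview) defines the endpoint: "The primary outcome in this study is the change in self-management, as measured through the Patient Activation Measure (PAM) questionnaire after 1 year", compared between users and nonusers of the digital PROM.

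Statistical Analysis makes this a continuous quantity: "The mean change will be estimated by subtracting the baseline scores from the follow-up scores". The group comparison follows: "Any differences in mean changes in short- and long-term variables will be modeled using an ANOVA". No covariate is attached to that ANOVA. The next sentence is the only place where an adjustment method is named: "To adjust for possible confounders, logistic regression models will include age, gender, and education". It gives no dependent variable.

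The groups are not randomised. Under Sample Size: "Consenting patients will be compared based on their chosen group, that is, engaged or not engaged in digital care". The same section concedes that "we can assume that there is a difference between patients who choose to engage in digital care and those who choose traditional health care services". The Limitations section offers, as protection against bias, "controlling for known confounders, and using appropriate statistical methods to analyze data in collaboration with a statistician".

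**The concern.** Logistic regression models a categorical outcome, most often a binary one. It returns an odds ratio, not a difference in mean PAM points. The model chosen to deal with confounding therefore does not fit the outcome that most needs it, and the model that does fit the outcome carries no adjustment.

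The same applies to PAID, WHO-5, EQ-5D, HbA1c and time in range, all recorded as scores or measurements at both T0 and T1.

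In a randomised trial this would be a minor slip. Here the Aims speak of evaluating the effect of participation, and patients choose their own group. Covariate adjustment is one of the few safeguards on offer, and the logistic regression sentence is the only one that turns the promise in Limitations into a method. An analyst following the text must report the primary comparison unadjusted, cut PAM change into a binary variable, or use a model that the protocol does not describe. That choice would then be open after the data are seen.

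**Working it through.** **Step 1. Match each model to what it can estimate.**

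| Element | In the protocol | Gives an adjusted difference in mean PAM change? |
|---|---|---|
| Outcome | PAM change, T1 minus T0, summarised as a mean | – |
| ANOVA | Group comparison, no covariates named | No: unadjusted |
| Logistic regression | Age, gender, education; no dependent variable named | No: needs a categorical outcome |
| Limitations | Known confounders to be controlled | No model named |

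**Step 2. Is there a declared binary PAM endpoint?** The four activation levels in Table 1 and the Self-Management section describe how to read the score. The change of at least 4 points under Sample Size is a threshold of clinical relevance. Neither is declared as a responder endpoint.

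**Step 3. The plan's own figure.** Sample Size requires 32 per group for a 4-point change, with no SD, alpha or power given, so it cannot be reproduced directly. Assuming two-sided 5% and 80% power, n = 2(1.96 + 0.842)² SD² / 4² with n = 32 gives SD = 4 / (2.802 × √(2/32)) = 4 / 0.7005 = 5.71. The target is thus consistent with a comparison of continuous means at an SD of about 5.7. That SD is implied, not stated, so larger values are shown as well.

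**Step 4. Possible shift in an unadjusted difference.** For one confounder, shift = (standardised imbalance between groups) × (correlation with PAM change) × SD of change. All three inputs are assumptions.

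| Imbalance | Correlation | SD 5.7 | SD 10 | SD 12 |
|---|---|---|---|---|
| 0.2 | 0.1 | 0.11 | 0.20 | 0.24 |
| 0.2 | 0.3 | 0.34 | 0.60 | 0.72 |
| 0.5 | 0.1 | 0.29 | 0.50 | 0.60 |
| 0.5 | 0.3 | 0.86 | 1.50 | 1.80 |

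The range is about 0.1 to 1.8 points against a threshold of 4.

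**Step 5. Cost of dichotomising to suit the logistic model.** Group sizes of 186 and 34 are from Results. Assumed: mean change 4 in users and 0 in nonusers, normal change scores, two-sided 5%, responder defined as a change of at least 4. The standard error of the mean difference is SD × √(1/186 + 1/34). The responder proportion is 0.5 in users and 1 − Φ(4/SD) in nonusers. Continuous power is from the t-test. Dichotomised power is from simulating the Wald test of the log odds ratio.

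| SD | SE of difference | Nonuser responders | Power, continuous | Power, dichotomised |
|---|---|---|---|---|
| 5.7 | 1.06 | 0.241 | 96% | 81–82% |
| 10 | 1.87 | 0.345 | 57% | 37% |
| 12 | 2.24 | 0.369 | 43% | 27% |

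A normal approximation for two proportions gives 82%, 38% and 28% in the last column.

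**The case against.** The strongest defence is that the dependent variable is left open.

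- **A model of user versus nonuser.** This would fit the aim of describing who engages, or could serve as a propensity model. It is a fair third reading beside an unadjusted ANOVA and a dichotomised outcome, so those two are not the only possibilities. But the text mentions no weighting, matching or stratification, and modelling who becomes a user does not by itself adjust the PAM comparison.
- **Loose wording.** Logistic may have been written where linear was meant, with a statistician involved and a fuller plan possibly in existence. That is plausible. Still, the article does not defer the adjustment model: it names one, and the name is wrong for the primary outcome.
- **Cut-points exist.** The 4-point change and PAID ≥40 are in the document, and some T1 variables, such as ketoacidosis, are categorical. Logistic regression has legitimate uses here. For PAM change, however, a threshold of relevance is not a declared endpoint.

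A reader might also infer that the primary estimate would carry the full selection bias. The documents do not support that. The outcome is change from baseline, which already removes stable differences in level between the groups, so only factors related to change remain. Nor would a linear model with age, gender and education remove all bias, since selection on motivation, for example, would persist.

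**Conclusion.** The point stands as a method stated wrongly. As written, no model in the protocol gives a confounder-adjusted difference in mean PAM change, so the commitment to control known confounders is not met for the primary outcome. The exceptions would be an undeclared dichotomy, which answers a different question with less power, or an unstated propensity model.

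The mismatch itself rests on no assumed number; its size does. The protocol gives no SD, imbalance or correlation. Over the assumed ranges, the shift from one confounder runs from negligible (0.1 points) to nearly half the 4-point threshold (1.8 points), and the upper end should not be quoted alone. The power loss from dichotomising is about 15 to 20 percentage points at each SD shown. A reader might conclude that the result will certainly be unadjusted or dichotomised. The text leaves that undetermined, which is itself the defect.

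**What to change.** In Statistical Analysis, replace the reference to logistic regression with a linear regression (ANCOVA) of PAM change on group, age, gender and education, plus any other prespecified confounders collected at T0. Apply the same form to the change in each other continuous outcome. Report the adjusted mean difference with its 95% CI as the main comparison and keep the ANOVA as the unadjusted companion.

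Add a model that also includes baseline PAM as a sensitivity analysis, not as the main one. In self-selected groups, conditioning on baseline can give a different answer from the change score that the protocol defines as its outcome. T0 may also not precede exposure for every user: the service began in November 2021, the first T0 was on October 27, 2022, and Table 3 records each participant's start date. For earlier starters, baseline PAM may already reflect part of the effect.

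Keep logistic regression for binary outcomes such as PAID ≥40, or for an explicitly stated model of who becomes a user. If that is a propensity model, say how it enters the PAM comparison.

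The cost is one or two sentences and a little more analysis. Age, sex, education and baseline PAM are already collected at T0, so no new data are needed. Confounding by unmeasured factors such as motivation will remain and should be acknowledged.
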